##### Mindfulness and Personality

Langer Mindfulness Scale (LMS)

The LMS is a 14-item questionnaire that assesses three sub facets of mindfulness: (1) novelty seeking (i.e., having an open and curious orientation to the environment), (2) novelty producing (i.e., an individual’s tendency to create new categories rather than relying on those previously formed) and (3) engagement (i.e., the ability to attend to changes in the environment) [77]. Participants are asked to answer the items on a 7-point Likert scale ranging from “Disagree” to “Agree”. The LMS has adequate internal consistency and temporal stability, and correlates appropriately with other instruments assessing theoretically-related constructs [78].

Five Facet Mindfulness Questionnaire

This 39-item self-report questionnaire was used to assess five different facets of mindfulness, namely observing, describing, acting with awareness, non-judging of inner experience, and non-reactivity to inner experience [79].

Big Five Inventory

This is used to measure five different dimensions of personality and each of these five different dimensions of personality is subdivided into six personality facets [80,81,82].

#### 2.6.4. Adaptive Responses to Energy Restriction

##### Energy Intake, and Factors Influencing it

Food Diary

Participants were provided with detailed written and verbal instructions prior to completing 7-day estimated food diaries which were reviewed for completeness by a dietitian [83]. These food diaries were used for data collection, as well as to aid in administration of the weight loss interventions. The food diary that was collected from −1 to 0 weeks was used to tailor dietary counselling to each individual participant. At all other time points, the food diary was used to monitor adherence (i.e., servings of food groups, number of meal replacement products consumed per day, etc.), and to provide individualized feedback to participants about their progress. Food diaries were coded and analyzed for nutrient composition and food group serves by trained dietitians, using a standardized protocol and FoodWorks Professional version 8 (Xyris Software, Brisbane, QLD, Australia).

Drive to Eat

General Food Craving Questionnaire—State (G-FCQ-S)

The G-FCQ-S assesses state-dependent cravings for tasty foods in general. That is, it assesses whether general food cravings are experienced in response to specific, momentary situations or psychological and physiological states [84].

Eating Self-Efficacy Scale (ESES)

The ESES is a 25-item scale that rates the likelihood of having difficulty controlling overeating across two factors; one concerned with eating when experiencing negative affect; and the other with eating during socially acceptable circumstances [85,86]. Two items (item 1 and 10) on the questionnaire were modified: (1) “Overeating after work or school” was changed to “Overeating after work or school *(or after your day’s activities, if you do not go to work or school)*”, as the original version may not be applicable to participants that are not working or at school; (10) “Overeating with family members” was changed to “Overeating with family members *(or with other people, if you do not eat with family members)*”, as the original version may not be applicable to participants that do not (regularly) eat with family members.

Subjective Drive to Eat (Visual Analogue Scales)—Fasting and Postprandial

Subjective appetite perceptions were measured at −20, 0, 15, 30, 45, 60, 90, 120 and 180 min in relation to completion of a standardized breakfast using an Electronic Appetite Rating System (EARS) that has been validated against the pen-and-paper version [87]. The breakfast consisted of a wholemeal English muffin (Tip Top, Enfield, NSW, Australia), 2 eggs (~60 g each, cooked by scrambling in a non-stick pan), 15 g of olive oil spread (Coles Supermarkets Australia Pty Ltd., Hawthorn East, Victoria, Australia), which was used to spread on the muffin and to scramble the eggs, 200 mL orange juice (Just Juice, Docklands, Victoria, Australia) and 300 mL tap water. The meal amounted to ~700 g and ~1900 kJ (~450 kcal). Participants were asked to complete the meal within 10 min, and to rate perceptions of hunger, fullness, how much food they felt they could eat (prospective consumption), desire to eat, and satisfaction, using the EARS tool. Participants move the cursor along a horizontal 100 mm visual analogue scale, anchored at each end with the statements “Not at all” or “None at all” (0 mm) and “Extremely” or “A large amount” (100 mm), to a point on the horizontal line that reflects the intensity of their current state. Gastrointestinal and other symptoms, namely nausea, bloating, irritability, and alertness, were also assessed.

Appetite-Regulating Hormones—Postprandial and/or Fasting

The venous cannula that was inserted for collection of fasting blood samples (for determination of serum markers of bone turnover and cardiometabolic health) was used to collect blood for plasma preparation and determination of appetite-regulating hormones. Venous blood sample collections were commenced at −18, 32, 62, 122, and 182 min relative to completion of the above-mentioned standardized breakfast (i.e., immediately after measurement of subjective drive to eat, which took approximately 1 min). The blood was collected into ice-cold EDTA-treated tubes (BD, Australia New Zealand, North Ryde, NSW, Australia) containing inhibitors to prevent degradation of hormones. The inhibitors consisted of 1 mg Prefabloc^®^ (Roche Diagnostics, Castle Hill, NSW, Australia), 10 μL dipeptidyl peptidase-IV inhibitor (Merck Millipore, Burlington, MA, USA), and 10 μL protease inhibitor cocktail (Sigma-Aldrich, St Louis, Missouri, USA) per 1 mL whole blood. Immediately after collection, samples were plunged up to the neck into wet ice, and were centrifuged as described above in the section entitled *Markers of Bone Turnover*. Immediately after centrifugation, aliquots of plasma were stored at −80 °C until subsequent analysis of ghrelin and peptide YY (in fasting and postprandial plasma samples) and leptin (in fasting plasma samples only).

Ketones

β-Hydroxybutyrate (Whole Venous Blood)

Fasting venous blood from the cannula was used to measure concentrations of circulating ketones (β-hydroxybutyrate) using β-ketone test strips and a ketone monitor (FreeStyle Optium, Abbott Diabetes Care Ltd., Witney, Oxon, UK), as per the manufacturer’s protocol.

Acetoacetic Acid (Urine)

Urinary acetoacetic acid concentrations were estimated using over-the-counter reagent strips (Ketostix^®^, Bayer Vital GmbH, Leverkusen, Germany), which determine the presence of acetoacetic acid upon reaction with nitroprusside salt. The end of the strip was dipped into a fasting urine sample collected from the participant soon after they arrived at our clinical research facility. The colour of the reagent strip was then compared to the color chart provided with the product, at 15 s after contact with urine.

##### Physical Activity

Self-Efficacy to Regulate Exercise

This scale describes eighteen situations that can make it difficult to maintain an exercise routine, and assesses an individual’s confidence in their ability to perform their exercise routine regularly (three or more times a week) during these situations [85]. For each item, participants indicate their confidence to execute the behavior on a 100-point percentage scale comprised of 10-point increments, ranging from “Cannot do at all” (0%) to “highly certain can do” (100%).

Pedometer Step Count and Physical Activity Diary

Participants were given a calibrated pedometer (Omron Walking Stle HJ-203, Omron Healthcare Co Ltd., Kyoto, Japan) to be worn in a pocket or bra, and were advised to gradually increase daily step counts to a total of 8000–12,000 steps per day, including 30–60 min per day of moderate to vigorous physical activity. This recommendation was based on achieving 200–300 min per week of physical activity, as recommended in the 2009 American College of Sports Physicians physical activity guidelines for weight loss and prevention of weight regain in adults [88]. Participants were asked to record the number of steps displayed on their pedometer in a daily physical activity diary for 7 days. This was done in their food diary, which contained spaces for recording physical activity (and sleep). This diary was thus referred to as the food, activity, and sleep diary.

Accelerometry

Intensity and duration of daily physical activities, as well as sleep, were measured using an accelerometer (SenseWear Pro Armband^®^, BodyMedia Inc, Pittsburgh, PA, USA) [89]. Participants were asked to wear the accelerometer continuously for 7 days, on the back of the upper tricep muscle of the left arm, except when showering or for water-based activities (e.g., swimming) as the device is not water proof. Participants were asked to record the time and reasons for taking off the accelerometer in their food, activity, and sleep diary.

##### Sleep (in Addition to Accelerometry)

Sleep Diary

Participants were asked to record in their food, activity and sleep diary, for seven days, what time they woke up in the morning (which may be different from the time they actually got out of bed), what time they tried to go to sleep the previous night (which may be different from the time they got into bed), and approximately how long (in minutes) it took them to fall asleep the previous night.

Epsworth Sleepiness Scale (ESS)

The ESS consists of eight self-report items, each scored from 0–3, that measure a person’s habitual “likelihood of dozing or falling asleep” in common situations of daily living [90,91]. No specific time frame is specified. The ESS score represents the sum of individual items, and ranges from 0–24. Values >10 are considered to indicate significant sleepiness.

Pittsburgh Sleep Quality Index (PSQI)

The PSQI is a 19-item self-report questionnaire for evaluating subjective sleep quality over the previous month, combined into seven clinically-derived component scores, each weighted equally from 0–3 [92]. The seven component scores are added to obtain a global score ranging from 0–21, with higher scores indicating worse sleep quality.

##### Energy Expenditure

Resting Energy Expenditure (REE, Indirect Calorimetry)

REE was measured via indirect calorimetry using a ventilated hood system (TrueOne2400, ParvoMedics, Inc, Sandy, UT, USA) after an overnight fast. REE was measured with participants lying in a comfortable supine position, with their head on a pillow and a transparent ventilated hood placed over their head. Plastic sheeting attached to the hood was tucked around the participant to form a seal between the air inside and outside the hood. Participants lay in a quiet room with an ambient temperature of ~23–25 °C. The ventilated hood system was calibrated before each measurement using standardized gases and rates of airflow, according to the manufacturer’s manual. Volumes of oxygen inspired and carbon dioxide expired were recorded continuously for 45 min, and the first 10 min of data were disregarded, as during this time the participant is considered to be adapting to the hood. REE (kJ/day) was calculated using the modified Weir equation, as previously published [93].

Body Temperature

Body temperature was measured over seven days using the same accelerometer used to measure physical activity and sleep, as described above. Body temperature was measured as it provides an indication of energy expenditure in a variety of mammalian species, including humans [94].

##### Neuroendocrine Status

As the hypothalamo-pituitary-adrenal, -thyroid, -gonadotropic, and -somatotropic axes are influenced by weight loss and are known to influence body composition if sustained for several weeks [15], serial measurements of hormones within these axes will demonstrate whether there is any differential effect of the FAST versus SLOW intervention on the concentrations of hormones that could adversely affect body composition, as well as the duration of any such changes. A suite of hormones will be measured to allow a more accurate assessment of whether the activity of each axis has been differentially altered by either intervention. Venous blood samples were collected either into serum tubes (BD, Australia New Zealand, North Ryde, NSW, Australia) and allowed to clot at room temperature, or collected into ice-cold EDTA-treated tubes (BD) and immediately plunged up to the neck into wet ice. Serum and plasma were obtained by centrifugation of blood samples as described above in the section entitled *Markers of Bone Turnover*, and aliquots were pipetted into CryoPure^®^ tubes and immediately stored at −80 °C until analysis. Serum and plasma samples were used for analysis of cortisol and adrenocorticotropic hormone, respectively, as indices of activity of the hypothalamo-pituitary-adrenal axis. Serum samples were used for analysis of free triiodothyronine or 3,3′,5-triiodothyronine (T3), reverse T3, free thyroxine or 3,5,3′,5′-tetraiodothyronine (T4), and thyroid stimulating hormone (TSH), as indices of activity of the hypothalamo-pituitary-thyroid axis; estradiol and sex hormone binding globulin, as indices of activity of the hypothalamo-pituitary-gonadotropic axis; and insulin-like growth factor-1 and insulin-like growth factor binding proteins, as indices of activity of the hypothalamo-pituitary-somatotropic axis.

##### Miscellaneous

Energy Homeostasis Questionnaire

This was a custom-built, experimental questionnaire in which we aimed to determine whether an individual’s propensity to lose weight or keep it off, or to mount adaptive physiological responses to energy restriction or energy excess, could be predicted by self-report of traits such as hunger, energy levels or body temperature after periods of relatively reduced or increased energy intake.

#### 2.6.5. General

##### Preferred Intervention

We asked participants to select 1 of 3 statements that best reflected how they felt when they found out which of the two interventions they had been randomized to. The statements were “I was disappointed”, “I was pleased”, and “I would have been pleased to have been randomized to either of the two diets”, with the different options listed in random order for each participant. This was asked in order to ascertain whether being randomized to the preferred intervention had any effect on the amount of weight that a participant lost on that intervention.

##### Diet Side Effect Questionnaire

The aim of this custom-built questionnaire was to capture and quantitate any side effects from the FAST intervention.

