### 2.2. Interventions

Eligible participants were randomized to either a “FAST” or “SLOW” weight loss intervention. The FAST intervention involved a total meal replacement diet (KicStart^TM ^meal replacement products [shakes and soups] from Prima Health Solutions Pty Ltd., Brookvale, NSW, Australia) involving severe energy restriction (target range for energy restriction was 65–75% relative to estimated energy expenditure) for 16 weeks, or until a BMI of no lower than 20 kg/m^2^ was reached, whichever came first, followed by slow weight loss (as for the SLOW intervention) for the remaining time up until 52 weeks (FAST intervention). The SLOW intervention involved a food-based, moderately energy-restricted diet (target range for energy restriction was 25–35% relative to estimated energy expenditure) for a total of 52 weeks. As such, we aimed for a minimum difference in energy restriction between women in the FAST versus SLOW interventions of 30% of estimated energy expenditure. The SLOW intervention was based on the Australian Guide to Healthy Eating (AGHE) [46], which provides recommendations as to the average number of standard serves of the five core food groups (vegetables, fruits, grains and cereals, meat and meat alternatives, reduced fat dairy) an individual should consume in order to meet their nutritional requirements, based on age and sex. In order to simplify adherence to the SLOW intervention in the TEMPO Diet Trial we defined six food groups. The meat and meat alternative and reduced fat dairy core food groups were collapsed into a ‘proteins’ group, and starchy vegetables were incorporated into the grains and cereals group to form a ‘carbohydrates’ group while also having a vegetables, fruits, fats, and discretionary foods group. For the FAST intervention, prescribed daily carbohydrate intake was less than 100 g. A protein intake of 1.0 g per kg of actual body weight per day was prescribed for both interventions. As it is not possible to achieve a protein intake of 1.0 g per kg using meal replacement products alone, without increasing energy and carbohydrate intake above target levels for the FAST intervention, the total meal replacement diet (KicStart^TM^) was supplemented with a whey protein isolate (Beneprotein^®^, Nestlé HealthCare Nutrition Inc, Florham Park, NJ, USA). The development process and rationale behind the dietary interventions for the TEMPO Diet Trial, as well as full details of the dietary interventions, have been published previously [47].

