In addition to attending our clinical research facility for data collection, participants were required to attend 21–22 individual dietary appointments with the trial dietitian ([name] or [name]). The initial individual dietary appointment at week 0 was scheduled for approximately 90 min, which is also when participants in the FAST intervention received their first meal replacement products (shakes and soups) and protein supplementation as required [47]. Subsequent individual dietary appointments (for review) were scheduled for 30 min approximately every 2 weeks for the first 26 weeks of the intervention (i.e., at 1, 2, 4, 6, 8, 10, 12, 15, 16, 18, 20, 25, and 26 weeks relative to commencement of the dietary interventions, plus an extra appointment at 17 weeks for participants in the FAST intervention during their transition from the FAST to the SLOW intervention), and then approximately every month until 52 weeks (i.e., at 29, 33, 37, 41, 45, 51, and 52 weeks). To increase compliance with individual dietary appointments, participants were able to complete appointments that did not require face-to-face contact (i.e., to collect a food, activity, and sleep diary or to collect meal replacement products and protein) via telephone. After 52 weeks, participants were given the option of attending monthly group support meetings of 60–90 min in duration each, facilitated on a rotating basis by different members of the research team ([name], [name], [name], [name] and [name]), sometimes in association with a guest facilitator.

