## 4. Conclusions

To our knowledge, the TEMPO Diet Trial will be the first randomized controlled trial to compare the long-term effects of fast weight loss (achieved via VLED in a total meal replacement diet involving severe energy restriction) to slow weight loss (achieved via a conventional food-based diet involving moderate energy restriction) on gold-standard measures of musculoskeletal integrity and eating disorder behaviors. This work has the potential to advance the treatment of obesity by providing information about the safety or otherwise of dietary obesity treatments that induce fast versus slow weight loss.

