**Exclusion Criteria**
Not ambulatory, or having restrictions to physical movement that would impede completion of trial activities
Osteoporosis
Extreme anemia that could be exacerbated by very low energy/total meal replacement diet
Hyperthyroidism or hypothyroidism
Diabetes mellitus (defined by fasting blood glucose level ≥7.0 mmol/L and glycated hemoglobin (HbA_1c_) ≥6.5%) [45]
Cardiovascular disease
Gastrointestinal disease
Previous gastric or other surgery that may affect appetite
Any loose metal in the body (e.g., pacemaker or bullet) that is contraindicated for magnetic resonance imaging (MRI) for safety reasons, or which may result in artefacts in medical imaging
Planning to undertake any major surgery in the next three years
Tobacco use
Alcohol or drug dependency
Taking medication that affects heart rate, body composition or bone mass (e.g., beta-blockers, glucocorticoids)
Having taken anti-resorptive therapy within the last three years
Having taken medication that affects appetite, metabolism, or weight within the past 6 months
Any of the following contraindications for following a very low energy/total meal replacement diet: lactose intolerance; following a strict vegan diet; or unwillingness to be randomized to one of the two diets
Donated whole blood within three months prior to commencement on the trial
Hepatic or renal impairments (which can be contraindications for following a very low energy/total meal replacement diet)

**Table 2 healthcare-06-00085-t002:** Outcomes measured at each time point during the TEMPO Diet Trial.

Time (Months) from Start of Dietary Intervention	~0			~0.25	~1	~4			~6			~12		~24		~36	
Time (Weeks) from Start of Dietary Intervention	−2	−1	0	1	4	15	16	17 ^§^	25	26	29	51	52	103	104	155	156

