**General**																	
Preferred Intervention			X														
Diet Side Effect Questionnaire				X	X												

§ Only measured in participants in the FAST intervention. *⌘* While food diary data was collected at 8–9 time points, the food diaries served the dual purpose of providing data for analysis, as well as assisting with adherence to the prescribed dietary intervention. † The Eating Disorders Examination Questionnaire and the Loss of Control Over Eating Scale were additionally collected at 8, 12 and 20 weeks. All samples of blood and urine are collected in the fasting state unless otherwise stated, and except for the urine sample taken after deuterium administration for determination of total body water. All pedometer and accelerometer measures, as well as food, activity, and sleep diaries, were commenced a week prior to the measurement time point. DXA, Dual-energy X-ray absorptiometry; ^1^H-MRS, proton magnetic resonance spectroscopy; MRI, magnetic resonance imaging.

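### The questionnaire meant to capture any side effect of FAST is scheduled only at weeks 1 and 4, so it misses the last 12 of up to 16 meal-replacement weeks and the return to food

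*Protocol article*

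**What the plan says.** The section on the Diet Side Effect Questionnaire gives the instrument one purpose and no time limit: "The aim of this custom-built questionnaire was to capture and quantitate any side effects from the FAST intervention".

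Section 2.2 (Interventions) defines FAST as total meal replacement "for 16 weeks, or until a BMI of no lower than 20 kg/m^2^ was reached, whichever came first". After that phase, FAST participants move to the food-based diet of the other arm until week 52. Section 2.3 (Study Protocol) lists the individual dietary appointments, "plus an extra appointment at 17 weeks for participants in the FAST intervention during their transition from the FAST to the SLOW intervention".

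Section 2.3 presents Table 2 as the schedule of all outcome measures. In the block headed General, the questionnaire row has two marks, under weeks 1 and 4. The footnotes add collections at weeks 8, 12 and 20 for two other instruments, the EDE-Q and the LOCES, but none for this one. The only column that a footnote restricts to FAST is week 17.

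**The concern.** An instrument meant to record any side effect of a diet needs to be in use while the diet is followed and when it ends. This one stops a quarter of the way through the meal-replacement phase. As scheduled, it cannot register symptoms that build up with longer exposure or that appear when food is reintroduced. A reader of the results could take its silence after week 4 as evidence that the diet was well tolerated, when the question was not asked.

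There is also no administration before the diet starts, so change from baseline cannot be calculated on this instrument.

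**Working it through.** The article states no coverage figure, so there is none to reproduce. The check is a reading of the schedule followed by simple arithmetic.

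**1. Placing the marks.** The Table 2 header row "Time (Weeks) from Start of Dietary Intervention" has 17 columns: −2, −1, 0, 1, 4, 15, 16, 17, 25, 26, 29, 51, 52, 103, 104, 155, 156. Splitting the rows at their column breaks gives:

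| Row | Weeks marked |
|---|---|
| Diet Side Effect Questionnaire | 1, 4 |
| Preferred Intervention (alignment check) | 0 |
| Subjective drive to eat (visual analogue scales) | 0, 1, 4, 16, 17, 26, 52, 104, 156 |
| DASS-21 | −2, 1, 4, 16, 17, 26, 51, 103, 155 |
| EDE-Q and LOCES | −2, 4, 16, 26, 29, 51, 103, 155, plus 8, 12 and 20 by footnote |

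The Preferred Intervention row falls at week 0, as expected, so the alignment is sound.

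**2. Share of FAST after the last administration.** With the last administration at week 4 and a phase of T weeks, the uncovered share is (T − 4)/T.

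- Full meal-replacement phase, T = 16: (16 − 4)/16 = 12/16 = 75%.
- Whole 52-week FAST intervention: (52 − 4)/52 = 48/52 = 92%.
- Return to food, from week 16 or earlier if the BMI limit is reached: no administrations.

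A participant who reached the BMI limit early would have a shorter gap. For illustration, T = 12 gives 8/12 = 67% and T = 8 gives 4/8 = 50%.

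**3. Could recall close the gap?** The recall period is not given. Whatever it is, a form completed at week 4 cannot look back on weeks 5 to 16.

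**4. Was there an opportunity?** Section 2.3 lists dietary appointments at weeks 6, 8, 10, 12 and 15, then 16, 17 (FAST), 18, 20, 25 and 26. The EDE-Q and LOCES were already collected at weeks 8, 12 and 20. The gap is not explained by lack of contact.

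**5. What else is measured in the gap?** The section on subjective drive to eat says that nausea, bloating, irritability and alertness were also assessed. Assuming they were rated whenever the appetite scales were, they have a week-0 value, an end-of-diet value at week 16, a FAST-only value at week 17 and a value at week 26. They cover four symptoms, are tied to a test breakfast, and have no mark between weeks 4 and 16. The DASS-21, EDE-Q and LOCES measure mood and eating pathology. Between weeks 4 and 16, therefore, the article shows no general side-effect measure.

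**The case against.** The strongest reply is that this is one ancillary questionnaire, listed under General and not a primary outcome, and that the word any may refer to type of side effect rather than time. On that reading there is no contradiction, only a loosely worded aim. It is true that the article states no period. But the aim names the FAST intervention as a whole, and the schedule stops at week 4 of a phase lasting up to 16 weeks, so the mismatch remains.

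Several stronger readings are tempting, and the document does not support them:

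- **That side effects go unobserved after week 4.** A reader might infer this from the questionnaire row alone. The four symptom ratings at weeks 16, 17 and 26 and the mood and eating questionnaires show otherwise. The gap belongs to this questionnaire, not to the whole trial.
- **That adverse events are not recorded.** General adverse-event recording may sit in the full protocol, which an article condenses. Its absence here is not at issue.
- **That the trial's safety conclusion fails.** Section 4 speaks of "providing information about the safety or otherwise of dietary obesity treatments that induce fast versus slow weight loss", but its preceding sentence, like the Discussion, ties safety to musculoskeletal integrity and eating-disorder behaviours. Table 2 follows those outcomes to weeks 155 and 156. Section 4 makes no tolerability claim and needs no change.
- **That symptoms present before the diet will be attributed to it.** The items are not shown and may ask about symptoms new since starting. Without a week-0 value this cannot be checked on the instrument, but the harm is not established.
- **That only FAST completes the questionnaire.** Nothing in Table 2 restricts the row to FAST. If both arms completed it, the randomised comparison at weeks 1 and 4 lessens the missing-baseline problem. It would remain if symptoms were attributed to FAST from that arm alone.

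**Conclusion.** The point holds as a mismatch between aim and schedule. For a participant who completes 16 weeks, 75% of the meal-replacement phase lies after the last administration. No administration covers the return to food, and there is no week-0 value. Other instruments fill this only in part.

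The conclusion rests on reading Table 2 as the complete schedule for this questionnaire, as Section 2.3 presents it. The number of side effects missed cannot be estimated from the document. No primary outcome is affected. What is limited is any statement about tolerability that draws on this questionnaire beyond week 4.

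**What to change.** **Where collection is still possible:** give the same questionnaire to both arms at week 0 and at existing appointments in weeks 8, 12, 16, 17 (FAST only), 20 and 26. Compare change from week 0 between arms, with week 17 described in FAST alone. The cost is a few minutes per appointment, with no new visit.

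**Where it is not possible:** this is the likely case. Recruitment ended in July 2016, so the last women randomised reached week 26 about half a year later.

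- Restate the aim of the questionnaire, and any tolerability statement based on it, as side effects in the first 4 weeks.
- Compare the arms at weeks 1 and 4 if both completed it. If only FAST did, say so and report the results descriptively.
- Report change from week 0 in nausea, bloating, irritability and alertness by arm at weeks 16 and 26, with week 17 for FAST only. Label this as limited later evidence from ratings made around a test breakfast.

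This route costs a narrower claim and one additional analysis of data already scheduled.
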